### Baseline measurement

When a potential participant responded to one of our calls, he or she was contacted by phone. During this initial contact the background and proceedings of the proposed study were explained by protocol. When the potential participant agreed to partake in this study an informed consent was sent by ordinary mail which he or she was required to sign and return by ordinary mail within one week. In addition, an e-mail was sent containing a hyperlink to the baseline questionnaire, which he or she was required to complete within one week. This baseline questionnaire gathered information of each participant on demographic variables, physical characteristics, sports & injury history, use of preventive measures, details and injury mechanisms of the current ankle sprain, and subsequent treatment and/or rehabilitation.

In order to create similar groups with respect to the outcome measures, participants were stratified by treatment, i.e. (para-)medical treatment or other/no treatment. As gender has never been identified as a factor related to secondary ankle sprain complaints, this was not a parameter for stratification. The participant was randomized to any of the three study groups and received oral and written instructions for the specific group allocation directly after completion of usual care.

### Follow-up measurement

Follow-up measurements commenced after randomization, and took take place once a month for a total period of 12 months. The monthly questionnaires gathered information on sports participation, on the use of preventive measures and sustained injuries to the lower extremities in the preceding month. Per training or match session the total minutes of participation were registered. Finally, the follow-up questionnaires measured residual complaints of the initial ankle sprain; pain, feeling of giving way and subjective restriction in range of motion of the ankle.

### Compliance

In a similar study compliance has been shown to significantly affect the effect outcomes of a preventive measure [17]. Therefore compliance to the allocated intervention protocol was measured through the monthly questionnaire. Participants in the neuromuscular training group were asked if they completed all (> 75%), most (more than 50%), a few (about 25%), or almost none of the prescribed training sessions during the 8 week intervention. Participants in the brace group were asked each month during follow-up whether they always (> 75%) wore the brace during sports, most of the time (more than 50%), a few times (about 25%), or almost none of the time during the prescribed period. Participants in the combination group were asked both questions during the 8 week intervention. After cessation of the prescribed intervention period participants were asked, as part of the monthly follow-up questionnaire, if they had performed additional neuromuscular training or wore a brace by own initiative.

### Injury registration

When a participant sustained an ankle injury during the follow-up period, the participant acknowledged this by e-mail. As a fail safe, ankle sprain recurrences were also recorded through the monthly follow-up questionnaire. After an injury was registered, the participant received an injury registration form. This form contained detailed questions on the diagnosis, the cause, and the aetiology of the re-injury. Furthermore, the advised treatment and the person who treated the injury were registered. The same form has been previously employed successfully in ankle sprain prevention studies [11,15]. Based on this form, a cost diary was sent to the athlete.

To evaluate the cost-effectiveness of the different intervention interventions participants who sustained an ankle sprain received a cost-diary.

The cost-diary is a log, which registered all absence from work, school and other chores of life, and (para-)medical treatment (including use of medication) from the moment of injury onwards until full recovery. From these cost-diaries direct and indirect costs resulting from the sustained ankle sprain could be calculated for use in an economic evaluation.

### Cost-effectiveness evaluation

The aim of the economic evaluation was to determine and compare the total costs for subjects in all three trial arms, and to relate these costs to the effects of these groups.

The economic evaluation was performed from a societal perspective. Table 3 provides an overview of the costs collected [18,19]. Cost of the intervention included costs that were directly related to the implementation of the intervention programmes. These costs included for the neuromuscular training program, the written information materials, an instructional video, development and maintenance of an informational website, and the balance boards. For the brace group only the costs of the brace and maintenance of an informational website were taken into account.

**Table 3 T3:** Costs as applied in the economic evaluation

Costs	Cost (€)
Direct health care costs:	
General practitioner (mean cost of total visits)^	87.19
Physical therapist (per visit = 30 min)*	28.00
Sports physician (per visit = 30 min)*	80.00
Medical specialist (mean cost of total visits)#	89.24
Hospital costs (if seen by specialist)#	397.80
Alternative therapist (per visit)*	27.20
Emergency room (per visit) ^	197.12
Drugs‡	n.a.
Medical devices‡	
Tape (per roll)	4.00
Brace	79.50
Crutches (rent per week)	15.00
Indirect costs:	
Absenteeism from paid work (per day)§	n.a.
Absenteeism from unpaid work (per hour)*	7.94

€ 1.00 = $ 1.47 = £ 0.89 (d.d. 07-06-11)

* Costs according to Dutch guidelines

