**Figure 3 F3:**
[figure not shown]
**Rock ankle exercise board, Avanco Sweden**.

**Table 1 T1:** Exercise schedule

**Exc**.	*Week 1*			*Week 2*			*Week 3*			*Week 4*			*Week 5*			*Week 6*			*Week 7*			*Week 8*		
	***1***	***2***	***3***	***4***	***5***	***6***	***7***	***8***	***9***	***10***	***11***	***12***	***13***	***14***	***15***	***16***	***17***	***18***	***19***	***20***	***21***	***22***	***23***	***24***

**A**	1	1	1	1	1	1	1	1	2	2	2	2	2	2	2	2	3	3	3	3	3	3	3	3
**B**	1	1	1	1	1	1	1	1	1	1	1	1	2	2	2	2	2	2	2	2	2	2	2	2
**C**	1	1	1	1	2	2	2	2	3	3	3	3	3	3	3	3	3	3	3	3	3	3	3	3
**D**	1	1	1	1	2	2	2	2	3	3	3	3	3	3	3	3	3	3	3	3	3	3	3	3
**E**	1	1	1	1	1	1	2	2	2	2	2	2	3	3	3	3	4	4	4	4	4	4	4	4
**F**	1	1	1	1	1	1	1	1	1	1	1	1	2	2	2	2	2	2	2	2	2	2	2	2

The content of each training session is shown vertically from session 1 to 24 (session numbers are printed bold). The exercises in each session are numbered A to F, the number (1 to 4) describes the difficulty level. Explanation of the difficulty level is given in Table 2.

**Table 2 T2:** Exercise difficulty level

Exc.	Difficulty level	Exc.	Difficulty level
**A**	1. on even surface	**E**	1. on even surface; with handheld
	2. on even surface; eyes shut		2. on even surface; without handhold
	3. on balance board		3. on even surface; eyes shut and without handhold
**B**	1. on high surface; with handhold		4. on balance board
	2. on high surface; without handhold	**F**	1. on even surface; walking
**C**	Same 3 levels as exercise A		2. on even surface; jumping
**D**	Same 3 levels as exercise A		

Subjects allocated to the brace group received an Aircast A60 Ankle Support brace for free (Figure 4). This is a semi-rigid ankle brace, specifically designed for use during sports. The design incorporates a sleek stabilizer located on either side of the ankle. This stabilizer is molded at a 60 degree angle to help guard against ankle sprains and prevent rollover. The light-weight anatomic design fits in athletic footwear. The brace is applied and adjusted with a single strap that securely holds it in place. The A60 is available in three sizes: small, medium, and large, with left and right models to guarantee optimal fit. Participants were encouraged to wear this brace during all sports activities for the duration of the entire 12 months follow-up.

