# Costs according to DBC (Zorgautoriteit 2011)

‡ According to tariff of the Royal Dutch Society of Pharmacy

§ Indirect costs for paid work was calculated for each injured separately based on mean income of the Dutch population according to age and sex

^ According to cost research on self-reference to GP and ER [22]

Besides the cost of the intervention itself, direct health care costs were included: i.e. costs of care by a general practitioner, physiotherapist, massage therapist, alternative therapist, and care by a sports physician or other medical specialist (e.g., orthopaedic surgeon, general surgeon); hospital care; use of drugs (e.g., paracetamol/actaminophen, ibuprofen) and medical devices (e.g., crutches, tape, braces). The costs of drugs were estimated on the basis of prices recommended by the Royal Dutch Society of Pharmacy [19]. Also indirect costs resulting from a loss of production due to absenteeism from paid or unpaid work were included. Indirect costs for absenteeism from paid work were calculated using the friction cost approach of 4 months, based on the mean age and sex-specific income of the Dutch population [18,20]. Indirect costs for productivity loss of unpaid work, such as study and household work, costs were estimated at a shadow price of €7.94 an hour [18].

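### Own-initiative preventive spending by participants without a recurrence has no described route into the costs, so the cost-effectiveness ratios may be biased, probably in favour of training

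*Protocol article*

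**What the plan says.** The Cost-effectiveness evaluation section adopts a societal perspective and aims to compare total costs across the three arms. It defines the programme component as follows: "Cost of the intervention included costs that were directly related to the implementation of the intervention programmes". For the brace arm it adds: "For the brace group only the costs of the brace and maintenance of an informational website were taken into account". Below Table 3 it also counts direct health care costs in every arm, including "medical devices (e.g., crutches, tape, braces" and similar items; Table 3 prices a brace at 79.50 euro.

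The only source described for costs outside the programmes is the cost diary (Injury registration). It goes to participants who sustain an ankle sprain, runs from the injury to full recovery, and supplies the costs of that sprain.

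Preventive behaviour outside the allocated programme is recorded in two places:

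- Follow-up measurement: "The monthly questionnaires gathered information on sports participation, on the use of preventive measures and sustained injuries to the lower extremities". This general item covers all arms.
- Compliance: "After cessation of the prescribed intervention period participants were asked", within the monthly form, "if they had performed additional neuromuscular training or wore a brace by own initiative".

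Statistical analyses specifies intention to treat, compares costs both among injured participants and in the total population, and makes neuromuscular training, named there as the cheapest intervention, the reference for the cost-effectiveness ratios.

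**The concern.** The costs and the effects do not cover the same behaviour. If a participant allocated to training obtains a brace, any sprain it prevents is counted for the training arm. If that participant stays free of a recurrence, no described rule picks up the price of the brace. Uninjured participants count in the total-population comparison, so this is not confined to a subgroup that the analysis leaves out.

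The opportunity for such spending is unequal. The brace and combined arms receive a brace free of charge, and the training and combined arms receive a balance board. New brace purchases would therefore fall mainly on the training arm, and new training costs mainly on the brace arm. Training is the reference for both ratios, so an unrecorded cost there shifts both.

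**Working it through.** **The plan's own cost figure.** Sample size gives 99 per group for a 50 euro cost difference and an SD of 108 euro. With two-sided 5% and 90% power (neither the sidedness nor the power is stated, so both are assumed): n = 2 × (1.960 + 1.282)² × 108² / 50² = 98.05, rounded up to 99. The figure is reproduced. The point below disputes no stated number; it concerns what enters the costs.

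**Inputs**

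- Training programme: 25 euro (Sample size).
- Brace price B: 50 euro (Sample size) or 79.50 euro (Table 3). The article does not say which applies to the brace programme, so both are carried through separately.
- p = share of the training arm that buys a brace that is not costed. Not given; assumed.
- q = share of the brace arm that incurs the full 25 euro training cost without its being costed. Not given; assumed.
- The combined arm holds both items and is taken to buy neither again.

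**Programme gaps as costed**

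- Brace minus training: B − 25 = 25.00 (B = 50) or 54.50 (B = 79.50).
- Combined minus training: (25 + B) − 25 = B = 50.00 or 79.50.

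**Gaps with own-initiative spending included**

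- Brace minus training: (B + 25q) − (25 + pB). Training's advantage is overstated by pB − 25q.
- Combined minus training: B − pB. The overstatement is pB, which cannot be negative.

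**Size with no offset (q = 0)**

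| p | Omitted cost, B = 50 | Share of 25.00 gap | Omitted cost, B = 79.50 | Share of 54.50 gap | Share of combined-minus-training gap, either B |
|---|---|---|---|---|---|
| 10% | 5.00 | 20% | 7.95 | 15% | 10% |
| 20% | 10.00 | 40% | 15.90 | 29% | 20% |
| 30% | 15.00 | 60% | 23.85 | 44% | 30% |

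**Effect of an offset in the brace arm**

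- p = 20%, q = 20%: overstated by 10.00 − 5.00 = 5.00 (B = 50) or 15.90 − 5.00 = 10.90 (B = 79.50).
- p = 10%, q = 50%: 5.00 − 12.50 = −7.50, or 7.95 − 12.50 = −4.55, so training's advantage is understated.
- The sign changes where pB = 25q, that is at q/p = B/25 = 2.0 (B = 50) or 3.18 (B = 79.50).

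**Uptake needed to reverse which arm is cheaper on programme cost (q = 0)**

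- Against the brace arm: p above (B − 25)/B = 25/50 = 50%, or 54.50/79.50 = about 69%.
- Against the combined arm: pB would have to exceed B, so p above 100%, which is impossible with one brace each.

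**The case against.** Several objections stand and limit the point.

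- **Braces are not left out altogether.** They are costed as medical devices in every arm. The diary restricts this to re-injured participants between injury and recovery, so the gap concerns purchases outside that window, chiefly by participants without a recurrence. The word only in the brace-arm sentence contrasts the contents of two programmes and says nothing about training-arm purchases.
- **Own-initiative use is not asked of everyone throughout.** The Compliance item starts when the prescribed period ends. For the brace arm that period is all of follow-up: "Participants were encouraged to wear this brace during all sports activities for the duration of the entire 12 months follow-up". Only the general item in Follow-up measurement reaches all arms, and as described it records use, not purchase.
- **Use is not cost.** Co-intervention notes that one guideline advises a brace for 3 to 6 weeks after return to sport, so some training-arm participants may already own one.
- **Direction.** A reader might infer that training's advantage is overstated against both brace arms. The documents support this only for the combined arm; self-initiated training in the brace arm is equally uncosted. The opposite sign does need q to be at least 2.0 times p with each such participant incurring the full 25 euro, although many exercise levels in Table 2 need only an even surface. Overstatement is therefore the likelier direction, but it is not shown.
- **Size.** Dividing the 79.50 euro brace of Table 3 by the 25 euro gap of Sample size gives 32, 64 and 95% at 10, 20 and 30% uptake. This mixes two brace prices and is too high under either.

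It can also be argued that a condensed article leaves costing detail to the full protocol. That would answer a silent article. Here the article states its perspective, its population, its intervention-cost rule and its source for other costs, and together these leave the spending out.

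**Conclusion.** The point holds in a limited form. In a societal, total-population comparison, preventive spending on own initiative by participants without a recurrence has no described route into the costs, while its effect is counted. The ratios may be biased, probably in favour of training. The direction is certain only against the combined arm, provided p is above zero and that arm does not buy its items again.

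At an assumed 20% uptake without offset, 20% of the combined-minus-training programme gap and 29 to 40% of the brace-minus-training gap would be missing. These shares refer to programme cost alone; the costs of recurrent sprains come on top and are not modelled. It might be inferred that the omission could change which arm is cheapest. On programme cost that would need more than 50% or about 69% uptake against the brace arm and cannot happen against the combined arm, so the documents do not support it as a likely outcome. The effect on the size of both ratios is the reason to act.

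**What to change.** Add to Cost-effectiveness evaluation and Statistical analyses a two-sided sensitivity analysis that uses the monthly forms and covers participants with and without a recurrence:

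- Charge one brace to each training-arm participant who reports own-initiative brace use, except those whose baseline questionnaire shows brace use before the trial and those whose diary already contains a brace.
- Charge up to the 25 euro training cost to each brace-arm participant who reports own-initiative training, as far as the general preventive-measures item identifies it.
- Use one brace price for programme and purchase throughout, and state which.
- Report each charge alone and both together, with the resulting cost differences and ratios. Present each charge as an upper bound on that arm's omitted spending, because use rather than purchase is recorded.

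Charging the training arm alone would build the expected direction into the result. A new purchase question would come late, since recruitment closed in May 2011. The cost is a few lines in the costing rules and one extra analysis on data already collected. The downside is that purchase versus prior ownership remains partly assumed: baseline use is only a proxy for owning a brace.

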**Figure 2 F2:**
[figure not shown]
**Home based neuromuscular training program, exercises A to F**.

All participants of the neuromuscular training group received the same balance board (Figure 3) for free. Furthermore general written and visual information on the duration and intensity of the program were provided. In addition, a website was created including basic information on the project and a section only accessible for each group's subjects. The exercise frequency was, with three training sessions per week, consistent throughout the full eight weeks (Table 1). The six exercises (A tot F) become more challenging as the program progressed (Table 2).

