### Statistical analyses

To evaluate the success of the randomisation, baseline values were analysed for differences between intervention group and control group, using a chi-square for categorical data and a student's t-test for numerical data.

All analyses were carried out according to the intention-to-treat principle. Cox-regression analysis was used to compare ankle recurrence risk between the intervention groups, using a significance level of P < 0.05. Other variables were checked for confounding and/or effect-modification and were adjusted for accordingly. Absence from sports was tested between groups using a Mann-Whitney test, since absence from sports due to an injury is not normally distributed [11].

Mean direct, indirect and total costs were estimated and compared between the three groups, both for the costs per subject in the injured population and for the costs per subject in the total population. Because costs are not normally distributed, 95% confidence intervals for the differences in mean costs were obtained by bias corrected and accelerated bootstrapping (2000 replications) [21]. Differences in costs and differences in ankle sprain recurrences were compared against the cheapest intervention (neuromuscular training) in a cost-effectiveness ratio, which estimated for each other condition the additional cost to prevent one ankle sprain recurrence. Confidence intervals for the cost-effectiveness ratio were calculated with bootstrapping, using the bias-corrected percentile method with 5000 replications. Uncertainty regarding the estimate of this ratio was expressed on a cost-effectiveness plane.

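### Website development is charged to the training programme but excluded from the brace arm, which uses the same site, so the brace-minus-training cost is understated

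*Protocol article*

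**What the plan says.** The Cost-effectiveness evaluation section opens with one general rule: "Cost of the intervention included costs that were directly related to the implementation of the intervention programmes". It then itemises by arm.

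- Training programme: "the written information materials, an instructional video, development and maintenance of an informational website, and the balance boards".
- Brace arm: "For the brace group only the costs of the brace and maintenance of an informational website were taken into account".
- Combined arm: no separate list in the article.

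Two other sections show what was delivered. In the Interventions section, after Figure 2, the article reports that "a website was created including basic information on the project and a section only accessible for each group's subjects". In the Baseline measurement section, a participant randomised to any of the three groups "received oral and written instructions for the specific group allocation directly after completion of usual care".

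The Statistical analyses section states that differences in costs and recurrences "were compared against the cheapest intervention (neuromuscular training) in a cost-effectiveness ratio".

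**The concern.** A single costing rule is announced and then applied differently to two arms, and no reason is given. The word only makes this a stated exclusion, not an item lost when the article was condensed. The brace arm is charged for upkeep of the informational website, so the authors accept that the arm uses one, yet the cost of building it falls on training alone.

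The stakes lie in the economic comparison. Costs are listed as a secondary outcome, but cost-effectiveness is the second hypothesis and the sample size is derived from costs. The sums are small: the Sample size section gives a mean recurrent-sprain cost of €27, a training cost of €25 and a brace cost of €50. A few euros per head in the intervention cost are therefore not negligible.

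The planned bootstrap would not reveal the problem. A fixed amount per participant missing from one arm moves the mean cost difference and its interval together and leaves the width unchanged.

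**Working it through.** **Step 1: items charged against items used.**

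| Item | Charged to training | Charged to brace | Used by brace arm, according to the article |
|---|---|---|---|
| Website maintenance | yes | yes | yes |
| Website development | yes | no | yes: one site, with "a section only accessible for each group's subjects" |
| Written material | yes | no | written instructions given to every arm; whether they are an intervention cost is not stated |
| Video, balance boards | yes | no | not described as used, so charging training alone is proper |
| Brace | no | yes | yes |

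The mismatch is website development, with written material as a conditional second item.

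**Step 2: direction.** Let T be the training cost without shared development, d the shared development per head now charged to training, B the brace cost, and a the per-head share if development were spread over all users.

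- Rule as written: B − (T + d) = B − T − d.
- Shared across arms: (B + a) − (T + a) = B − T.
- Dropped from every arm: B − T.

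Both consistent rules give the same answer for the shared part, and the rule as written falls short of it by d. Any brace-specific instructions costing w per head that belong to the intervention add a further w to the shortfall. Write x for the total per head. The brace-minus-training cost is understated by x, one euro for one euro, in favour of the brace.

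**Step 3: possible size.** The article gives no price for website development or written material, so x is an assumption throughout. Inputs from the article are training €25 and brace €50 (Sample size section), and brace €79.50 (Table 3, medical devices). The article does not say which brace price the intervention costing uses, so both are shown. Assume the €25 already covers every listed training item.

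- Uncorrected difference: 50 − 25 = €25, or 79.50 − 25 = €54.50.
- Corrected difference: 25 + x, or 54.50 + x.
- Share of the corrected difference that is missed: x / (25 + x), or x / (54.50 + x).

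| Assumed x (€) | Corrected difference, brace €50 | Share missed | Corrected difference, brace €79.50 | Share missed |
|---|---|---|---|---|
| 0 | 25 | 0% | 54.50 | 0% |
| 5 | 30 | 16.7% | 59.50 | 8.4% |
| 10 | 35 | 28.6% | 64.50 | 15.5% |
| 20 | 45 | 44.4% | 74.50 | 26.8% |
| 25 | 50 | 50.0% | 79.50 | 31.4% |

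If the brace arm's share per head is similar to training's, x must lie below €25, because boards and video also sit within that sum. The last row is a bound that cannot be reached.

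**Step 4: effect on the ratio.** The numerator of the brace-versus-training cost-effectiveness ratio is too low by x. The denominator, the difference in recurrences, is untouched.

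**Step 5: ranking.** Under the Step 3 assumption the corrected difference is larger than the uncorrected one in every row, so training stays the cheaper of the two on intervention cost.

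**The case against.** The best defence is that the two lists reflect one rule after all. Training is an unsupervised home programme of six exercises over 24 sessions, and its content has to be conveyed by text, pictures and web pages. A brace is a device. The sentence about the website stands among the materials for the training group, and nothing says the brace section cost much to build. This stands in part: the arms need not carry equal amounts, and training-specific content belongs to training. It does not justify a brace share of exactly zero for a site that includes general project information and a section for each group. If development is instead regarded as sunk, it should leave every arm.

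The written instructions are weaker evidence. They are described under Baseline measurement and may be communication of the allocation, not the written information materials listed for training. That objection stands, so they count here only if they are part of the intervention.

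A reader might also infer that the uneven rule could erase or reverse the €25 price gap and so undermine the choice of training as the cheapest reference. The documents do not support this. It would need a per-head development cost above €25, which is stated nowhere, together with a planning figure of €25 that leaves development out and a brace priced at €50. If the €25 already includes development, correction widens the gap. At €79.50 the gap is €54.50, and development would have to exceed that. On any of these readings, correction moves the comparison further in training's favour than the rule as written does.

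**Conclusion.** The point holds for website development: the article excludes it from the brace arm by explicit statement, gives no reason, and elsewhere describes that arm as a user of the site. It holds for written material only on the condition that the brace instructions are part of the intervention.

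The direction is certain and favours the brace. The amount cannot be computed from the documents and may be small if development is spread over many users; the percentages above are illustrations under assumed values of x. Training remains the cheaper of the two at the planning prices if the €25 covers the listed items, so what is at risk is the size of the incremental cost and the ratio built on it, not the reference arm.

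If the combined arm carries the full training list plus the brace, the brace gains against that arm too. The article does not state the combined arm's rule, so this remains conditional.

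**What to change.** Replace the two unequal lists with one costing rule for all three arms.

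1. Either allocate shared website development per participant across every arm that uses the site, or drop it as a sunk cost from every arm. State which. The two agree on shared development but differ on arm-specific web content, which the first keeps with its arm and the second removes.
2. Charge arm-specific content to its own arm: video and balance boards to training, the brace to the brace arm, and each arm's own written material to that arm. Say whether the allocation instructions count as intervention material.
3. Cost the combined arm as both packages, with shared items counted once.
4. State the price used for the intervention brace, since €50 and €79.50 both appear.
5. Recompute the incremental costs and cost-effectiveness ratios on that basis.

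The cost is one revised paragraph and a re-tabulation of intervention costs. The development figure is already needed to cost the training arm, and no new participant data are required.
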